## Abstract

Background. A Cochrane review found that there is insufficient evidence to determine the effectiveness of acupressure for pain relief. One of the problems detected is the methodological variability reported. Objective. To assess the impact of the application of acupressure on obstetric and neonatal outcomes of labor, pain experience, and mother’s satisfaction with the experience. Method. Design of a protocol to carry out a two-arm multicenter single-blinded randomized controlled trial. Intervention (pressure on LI4 of the left hand, B6 of the left leg, GB21 of the left shoulder, and then the same sequence on the right side) and placebo (application of the technique on points not identified by acupuncture as key points) will be performed by a single researcher. Results. The recruitment began in April 2021 and, to date, there has been the participation of 40 women, divided into 17 included in the experimental group and 23 in the control. Communication of future results will be made in accordance with the CONSORT checklist. Conclusions. The designed protocol could methodologically improve some aspects of previous studies while maintaining adequate statistical power. The effectiveness of acupressure for one or more outcomes proposed (time and pain in labor) could support the inclusion of a new therapeutic tool in the clinical practice of midwives that would allow them to assist pregnant women, improving their experience both physically and psycho-emotionally

## 1. Introduction

Childbirth, being a natural phenomenon, encompasses various dimensions, making it a comprehensive and subjective experience in which physiological, psychological, social, and cultural factors come into play [1]. The perception of pain during the process is a key aspect, and it is worth noting that factors such as fear of pain, concerns about undergoing an episiotomy, and the fear of losing control over the situation have been identified as significant contributors to tokophobia, which is a psychological condition characterized by an intense fear of childbirth [2].

It is noteworthy that women exhibit a keen interest in exploring complementary forms of care that empower them to maintain a sense of control throughout the labor process [3]. Midwives also want offer alternatives and, consequently, non-pharmacological techniques for pain management during childbirth, as well as methods for labor induction or stimulation, have emerged as potential alternatives or supportive measures in the context of medicalized childbirth [4]. These approaches hold promise in providing women with additional options and support during childbirth, fostering a holistic approach to the birthing experience.

Different techniques developed in traditional Chinese medicine are used as alternative and/or complementary therapies in order to reduce the medicalization of healthcare. Some of these most-used techniques are acupuncture, acupressure, moxibustion (moxa), and transcutaneous electric nerve stimulation (TENS) on acupoints, and all have been applied to pregnant women for this purpose [5]. Within the realm of traditional Chinese medicine (TCM), qi represents the vital energy that traverses the body’s 14 pathways, commonly known as meridians. By employing techniques such as acupuncture and acupressure, it becomes possible to stimulate this energy and reinstate equilibrium and well-being. These techniques arose from the “gate theory”, in which it is believed that the stimulation of these points can stimulate the fibers that transmit impulses to the spinal cord. Specifically, acupressure consists of stimulating acupuncture points through the hands and/or fingers, as well as utensils such as awls and even ice [4,6].

The recent literature has provided affirmations regarding the potential benefits of applying pressure on acupuncture points in improving obstetric and neonatal outcomes. While there is a growing consensus on the effectiveness of this technique in reducing perceived pain during pregnancy, further investigations are still warranted to explore its impact on labor duration, maternal satisfaction, and associated neonatal outcomes. These types of outcomes are less explored and when, they are evaluated, they can be studied with different methods or partial and inconclusive results can be obtained [7,8,9,10].

Building upon this foundation, Haj and Xiao-Nong emphasized the need for standardized interventions to establish clear guidelines for the utilization of this technique and to demonstrate its utility [9]. Notably, a comprehensive Cochrane review conducted by Smith et al. in 2020 reported a lack of studies that conclusively confirm the positive impact of acupressure on pain relief due to limited available evidence. The review also identified challenges associated with variability in the selection of acupuncture points, diverse techniques employed, inadequate information on applied pressure and duration, as well as differences among therapists, which can introduce further variations in practice [10]. It is evident that further research and standardization efforts are essential to shed more light on the potential benefits and enhance the utilization of acupressure as a complementary approach in obstetric care.

Some of the most-used points in the literature were:Jianjing (GB21): Located in the middle of the imaginary line that joins the spinous process of the seventh cervical vertebra (C7) and the upper part of the shoulder joint (lateral end of the acromion). It is a point with sensation of heat or numbness. It is a point that reacts to pressure, and can generate an unpleasant sensation. This point is useful in the stage of fetal dilation and descent, and can stimulate uterine contractions [11,12,13].Hegu (LI4): Located between the first and second metacarpals (thumb and index bones). It is at the highest point seen when the thumb rests on the index finger. It acts as a stimulus for contractions if they are irregular, making them more efficient [14,15,16,17,18].Sanyinjiao (B6): It is located four fingers of the woman above the prominence of the medial malleolus (inside of the ankle). It is a pressure-sensitive area. This point helps the cervix to dilate more easily. Pressing can be stopped once labor has effective and regular contractions [1,11,12,15,16,19,20].Yongquan (R1): It is located in the depression found in the upper third of the sole of the foot (easily located when the foot is placed in plantar flexion, that is, flexing the fingers towards the sole of the foot). It is essential to apply forceful pressure, squeezing inwards and upwards, towards the first toe. It has a relaxing effect [21].Hand Points: These are located along the creases of the hands where the fingers join the palm. Helps release endorphins, which are natural pain relievers. The woman holds a small comb in the palm of her hand so that the teeth press on these points. She can squeeze the comb during contractions by pressing to get the desired effects [21].

In short, labor and the pain associated with this phase is something that worries pregnant women, manifested by the high demand for pharmacological methods for pain relief, so identifying non-pharmacological interventions that reduce or minimize this will allow a significant improvement in women’s satisfaction with the vital experience of childbirth. The midwife constitutes the cornerstone to achieve this purpose [22].

## 2. Objectives and Hypothesis

The general objective is to assess the impact of the application of acupressure on obstetric and neonatal outcomes of labor. To achieve the general objective, four specific objectives have been established, each based on the verification or refutation of a specific hypothesis.

Objective 1: To analyze the possible statistical association between the use of acupressure and the times of cervical dilation and fetal delivery.

Null hypothesis: The dilation time and the expulsive time in the women who receive the intervention is the same as those of the women in the control group.Alternative hypothesis: The time of dilation and the time of expulsion in the women who receive the intervention is not the same as those in the women in the control group.

Objective 2: To compare the pain perceived by pregnant women in relation to the use of the acupressure technique.

Null hypothesis: The pain experienced by women receiving the intervention is the same as that experienced by women in the control group.Alternative hypothesis: The pain experienced by women receiving the intervention is not the same as that experienced by women in the control group.

Objective 3: To study the relationship between the use of acupressure and maternal satisfaction regarding the childbirth experience.

Null hypothesis: The satisfaction experienced about the birth process in women receiving the intervention is the same as that in women in the control group.Alternative hypothesis: The satisfaction experienced about the birth process in women who receive the intervention is not the same as that in women in the control group.

Objective 4: Assess the safety of the intervention through fetal and neonatal outcomes.

Null hypothesis: The fetal and neonatal results of the pregnant women belonging to the intervention group are the same as those in the pregnant women of the control group.Alternative hypothesis: The fetal and neonatal results of the pregnant women who belong to the intervention group are not the same as those in the pregnant women of the control group.

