### 3.3. Sampling and Sample Size

The sampling process will be conducted using an intentional or convenience sampling approach, wherein all pregnant women who meet the inclusion criteria and are under the care of the project’s principal investigator will be included until the predetermined sample size is reached. This meticulous approach aims to encompass a diverse range of participants, thereby enhancing the generalizability of the study findings.

The calculation was based on the results obtained in a pilot study (unpublished data) with 17 and 23 women in the intervention and control groups, respectively, using the Gpower 3.1.9.4 software. Different calculations were carried out based on the means and standard deviations obtained in the times of the active, passive, and expulsive phases, as well as on the VAS scale (Likert 1–10 points) used to measure pain. From the different calculations carried out, the one that determined the largest sample size (difference of means in time of expulsive phase) was selected with the intention of having sufficient statistical power for all the analyses proposed.

The means and standard deviation obtained for the expulsive phase time (second stage of parturition, which starts at full dilation and continues until birth) in a pilot study were 46 ± 39 min for the intervention group and 65 ± 47 min for the control group. The number of women per group was calculated to determine a difference in the means of independent groups with alpha = 0.05 (type I error), power (1-beta) = 0.8, and allocation n1/n2 ratio = 1, obtaining a total of 166 women (83 in each group) [23].

Recruitment. The selection of participants for this study will adhere to specific criteria outlined as follows:

Inclusion criteria: The study will include pregnant women who meet the following requirements: Women with induced, accelerated, or spontaneous labor, both primiparous and multiparous, are included.Women who are 18 years of age or older and in the term of their pregnancy (37–42 weeks).Single gestation (not multiple pregnancies).Absence of associated pathologies or medical conditions.Proficient communication skills in the Spanish language.

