Independent variables.-Sociodemographic: Age (years), country of birth, weight (kg), height (cm), marital status (single, domestic partner, married, divorced, widowed), studies (primary, secondary, superior, postgraduate), employment (employed, unemployed), dysmenorrhea: yes/no (verbalization by the woman of having painful menstruations), fear of childbirth (yes/no), reasons for fear of childbirth (verbalization by the woman), hospital (public/private).-Clinics: date of last period (FUR) and probable date of delivery (FPP), gestational age (weeks of gestation), obstetric formula (pregnancies, abortions, childbirth), estimated fetal weight (kg), fetal weight at birth (kg), type of delivery termination (eutocic, instrumented, caesarean section), special circumstances associated with childbirth (maternal fever, meconium, cord prolapse, antepartum hemorrhage, and uterine rupture), factors associated with the newborn (abnormal registration and altered arterial pH, considering normal values—arterial pH at birth: 7.25–7.45, blood oxygen (PaO2): 60–80 mmHg, blood carbon dioxide (PaCO2): 35–45 mmHg, bicarbonate (HCO3-): 24–26 mEq/L, base excess: ±3.0).-Variables that can affect the effectiveness of the intervention: hospital shift the night before (yes/no), start time of application of the technique (0–24 h), level of saturation of the system (number of women in the service attended by the researcher).

Data analysis. The data obtained will be analyzed with IBM SPSS Statistics v23 software; this will allow for the descriptive analysis of qualitative variables through absolute frequencies and percentages, and of quantitative variables through measures of central tendency, dispersion, and position. On the other hand, a statistical inference analysis will be carried out to evaluate the possible differences between the groups; these will be treated as unpaired samples because there are different women who constituted each group.

The statistical association between qualitative variables will be analyzed using Pearson’s chi-square test or Fisher’s exact test (in 2 × 2 tables when in Pearson’s Chi square, the expected frequencies are less than 5 in more than 20% of the cells). Odd ratio will be calculated as size effect measure for this analysis.

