## 5. Discussion

The primary objective of this study’s protocol is to introduce a novel acupressure intervention, incorporating points that have been extensively studied in the scientific literature and have demonstrated their effectiveness. However, certain points located on the back were deemed impractical due to the supine position in which women typically find themselves during childbirth. Consequently, these points were excluded from the intervention. Conversely, we have identified points from Dávila’s doctoral thesis that have not been previously documented [21]. The strategic positioning of these points enables a more practical and feasible intervention approach. 

Based on the findings, it is anticipated that the meticulously chosen set of points, previously unexplored, will provide a prompt and effective intervention. We expect this intervention to yield improved perinatal outcomes while minimizing discomfort for the mother. By utilizing these previously unexplored points, we aim to optimize the intervention’s efficacy and enhance the overall childbirth experience for women. Therefore, the midwife should position the woman in the standard childbirth posture and can proceed with the intervention, as easy access to the proposed points is ensured in this position. This is crucial from an ergonomic perspective, benefiting both the pregnant woman and the midwife.

The outcomes derived from the implementation of this protocol possess the potential to generate significant and applicable insights for clinical practice, thereby enhancing the overall childbirth experience by reducing pain perception and duration. Consequently, such improvements would directly contribute to heightened satisfaction among women undergoing this crucial life event. Furthermore, if the safety of the intervention for both mothers and infants is demonstrated, its incorporation into the healthcare system of our country would carry substantial weight as a valuable tool for future implementation.

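### Safety is assessed by a test of no difference that cannot show safety; 83 women per arm gives little power for infrequent harms, and no maternal harm is among the outcomes

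*Protocol article*

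**What the plan says.** All references are to the protocol article.

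- **2. Objectives and Hypothesis.** Each objective is to be settled by confirming or rejecting its own hypothesis. Objective 4 concerns safety, judged on fetal and neonatal results. Its null hypothesis is "The fetal and neonatal results of the pregnant women belonging to the intervention group are the same as those" in the control group, and the alternative is that they differ. No margin is given.
- **3.3, Data analysis.** Every test uses the 5% level.
- **3.3, sample size.** Calculations were made for the phase times of labour and the VAS. The largest result, for expulsive time, was chosen "with the intention of having sufficient statistical power for all the analyses proposed". Its settings are "alpha = 0.05 (type I error), power (1-beta) = 0.8, and allocation n1/n2 ratio = 1", giving 83 women per group.
- **3.3, Outcomes.** The list is labour times, pain and analgesia, maternal satisfaction, and neonatal outcomes (Apgar and arterial blood gases). It contains no maternal harm.
- **3.3, Independent variables.** This list includes "special circumstances associated with childbirth (maternal fever, meconium, cord prolapse, antepartum hemorrhage, and uterine rupture" and also "factors associated with the newborn (abnormal registration and altered arterial pH", the latter with normal ranges for the blood gases.
- **5. Discussion.** Adoption by the healthcare system is supported "if the safety of the intervention for both mothers and infants is demonstrated".

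**The concern.** A test of equality can give evidence that two arms differ. When it does not reject, it leaves open every difference inside the confidence interval. With a safety objective resting on such a test, the result most likely to be read as reassuring is the one that carries least information. The smaller the trial and the rarer the harm, the more likely that result becomes.

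Three features of the plan add to this. The sample size took no account of any safety endpoint, although the power aim covers all analyses. The Discussion speaks of safety for mothers, but neither the safety objective nor the outcome list includes a maternal harm. And the harms that are recorded stand under a heading that does not mark them as outcomes, with arterial blood gas appearing in both lists.

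At stake is what the trial may say about safety, which the Discussion links to adoption. The efficacy comparisons are not affected.

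**Working it through.** **Step 1: reproduce the plan's sample size.** Inputs from section 3.3: expulsive time 46 ± 39 v 65 ± 47 min, two-sided alpha 0.05, power 0.8, ratio 1.

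- Common SD = √((39² + 47²)/2) = 43.19 min
- d = (65 − 46)/43.19 = 0.44
- Noncentral t with n = 83 per arm: noncentrality = 0.44 × √(83/2) = 2.83, 164 degrees of freedom, power 0.804

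The stated 83 per arm is reproduced. One-sided calculation would need only 65 per arm and does not match.

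**Step 2: the same 83 per arm for binary harms.** The article gives no event rates, so the rates below are assumptions. Power is the sum, over all pairs of event counts (i, j), of Bin(i; 83, p₁) × Bin(j; 83, p₂), taken where the two-sided Fisher p is below 0.05.

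| Assumed rates, control v intervention | Fisher power |
|---|---|
| 2% v 4% | 3% |
| 2% v 6% | 12% |
| 5% v 10% | 15% |
| 10% v 20% | 36% |
| 5% v 20% | 81% |
| 10% v 30% | 88% |

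Power is low for a doubling at any of these control rates. It becomes adequate only for excesses of 15 to 20 percentage points.

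**Step 3: two results that need no assumed rate.**

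- Five events in one arm and none in the other (6.0% v 0%) is not significant: two-sided Fisher p = 2 × (83·82·81·80·79)/(166·165·164·163·162) = 0.059.
- No events in 83 women leaves an upper limit for the true rate of 1 − 0.05^(1/83) = 3.5% (one-sided 95%) or 1 − 0.025^(1/83) = 4.3% (two-sided 95%).

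**Step 4: precision of a risk difference.** If both arms share a true rate p, the approximate 95% half-width is 1.96 × √(2p(1 − p)/83). This is 4.3 percentage points at 2%, 6.6 at 5% and 9.1 at 10%.

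**Step 5: continuous measures.** For mean arterial pH or base excess, 83 per arm has 80% power at d = 0.44 and 89% at d = 0.5. The 95% half-width is 1.96 × √(2/83) = 0.30 SD. This is useful precision, but a non-significant difference still excludes only what lies outside the interval.

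**Step 6: where each harm is placed.**

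| Item | Objective 4 | Outcomes | Independent variables |
|---|---|---|---|
| Apgar | yes (neonatal) | yes | no |
| Arterial blood gas / pH | yes (neonatal) | yes | yes |
| Maternal fever, antepartum haemorrhage, uterine rupture | no | no | yes |
| Meconium, cord prolapse, abnormal registration | not named | no | yes |

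No maternal harm appears in either place that defines what safety will be judged on, although the Discussion's conclusion includes mothers.

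**The case against.** Four stronger readings are tempting, and the article does not support them.

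- **That a non-significant result will be declared safe.** The Discussion is conditional, and nowhere is p > 0.05 said to count as safety. This is right. What stands is that the article settles each objective through its hypothesis, and the only safety hypothesis is equality. It offers no other criterion.
- **That the harms will never be compared between arms.** A reader might infer this from the heading over them. But Data analysis provides chi-square or Fisher tests with odds ratios for qualitative variables and plans inference on differences between groups, which could cover them. The fault is one of classification: nothing identifies them as safety outcomes.
- **That adjusting for these events would bias the treatment comparison.** No multivariable model is planned. The regression paragraph describes correlation coefficients only. Nor is it established that all these events follow treatment: women in induced, accelerated or spontaneous labour are eligible, and fever, meconium, antepartum haemorrhage or an abnormal registration could precede the first application.
- **That the missing acceptable margin is an error.** A margin is commonly left to the analysis plan, which is not shown.

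Two further objections have weight. The power figures depend on assumed rates and concern infrequent binary harms, whereas the listed neonatal outcomes are scores and continuous values, for which the trial is better placed. And the power sentence states an intention, not a result. As an intention it still extends to analyses that the calculation did not consider.

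**Conclusion.** The point holds within these limits. An equality test at 5% is unsuited to a safety objective, because its non-significant result cannot establish safety for binary or continuous outcomes.

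The size of 83 per arm is correct for expulsive time (power 0.804). For a doubling of an infrequent binary harm, power is about 3% to 36% at assumed control rates of 2% to 10%, so such a doubling would be missed in most trials of this size. The limits of 3.5% and 4.3% after no events in 83 women do not depend on assumed rates. For mean pH and base excess, power is 80% at d = 0.44, and the reservation there concerns interpretation more than precision.

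A conclusion about mothers has no maternal harm behind it in the objective or the outcome list, and arterial blood gas is classified twice. The efficacy conclusions are untouched. The plan should be changed on this point because it determines what may be claimed about safety.

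**What to change.** - **Objective 4:** report between-arm differences with 95% confidence intervals: risk differences for binary harms, mean differences for arterial pH and base excess. State that p > 0.05 will not be read as safety.
- **Outcomes:** list maternal fever, meconium, cord prolapse, antepartum haemorrhage, uterine rupture and abnormal registration as safety outcomes. Compare them by randomised arm, counting those with onset after the first application.
- **Arterial pH:** list it once, as an outcome.
- **Sample size:** restrict the power statement to labour times and VAS.
- **Discussion:** limit any safety conclusion, for mothers and for infants, to what the intervals exclude.

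The cost is wording and tables. The events and the start time of the technique are already listed for recording, and no more women are needed. The article does not say whether the onset of each event is noted; if it is not, that is one extra entry per event. The downside is a more modest safety conclusion.

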For the comparison of means between dichotomous variables, the Student t-test and ANOVA test will be performed in the case of dichotomous or polytomous variables, respectively, as long as the parametric criteria are met (normality evaluated using the Kolmogorov–Smirnov test and homoscedasticity evaluated with the Levene test). If the parametric criteria are not met, non-parametric tests will be performed (Wilcoxon test and Kruskal–Wallis test, respectively). For the Student t-test analysis, Cohen’s d will be used as a measure of the effect size. 

For regression analysis, the Pearson correlation coefficient will be used. In the case of non-normal distributions, Spearman correlation test will be used. Statistical significance at 5% will be established for all tests.

Ethical aspects. The present study preserves the well-being of the subject above the interests of science or society and the ethical considerations that support it, as part of the compliance with current international and national regulations for health research studies with human beings, as well as that referring to the protection of personal data and clinical information derived from it. Under these premises, this protocol has been approved by the Regional Ethics Committee (committee code 4928, project code: AcuP, approval date 24 February 2021, record number 319).

Data collection notebooks will be handled in which only identification codes will appear that will correspond to the personal data in other guarded records. Similarly, electronic database-type records will be designed disaggregated to avoid identification of patients. An Informed Consent document has been prepared. The intervention does not require invasive tests or manipulation of biological samples beyond those implemented in routine clinical practice.

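### Objective 4 tests neonatal safety against a null of equality, so the only result that could support a safety claim is a failure to reject, and that cannot demonstrate safety

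*Protocol article*

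**What the plan says.** Section 2 (Objectives and Hypothesis) sets four specific objectives, "each based on the verification or refutation of a specific hypothesis". The fourth is to "Assess the safety of the intervention through fetal and neonatal outcomes". Its null is "The fetal and neonatal results of the pregnant women belonging to the intervention group are the same as those" in the control group, and its alternative is that the results "are not the same as those in the pregnant women of the control group". This is the same two-sided template as for the three efficacy objectives.

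Section 3.3 (Outcomes) lists the neonatal outcomes as Apgar at 1, 5 and 10 minutes and arterial blood gases at birth. Section 3.3 (Data analysis) names Pearson's chi-square or Fisher's exact test for categorical variables, with an odds ratio, and the t-test or Wilcoxon test for means, with Cohen's d for the t-test. It adds: "Statistical significance at 5% will be established for all tests".

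The sample size paragraph of section 3.3 considers labor phase times and the pain VAS. It takes the largest result, from expulsive-phase time, with "alpha = 0.05 (type I error), power (1-beta) = 0.8, and allocation n1/n2 ratio = 1", "obtaining a total of 166 women (83 in each group"). The stated intention is that this number should be enough for every analysis proposed.

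Section 5 (Discussion) says that "if the safety of the intervention for both mothers and infants is demonstrated", bringing the technique into the health system would carry substantial weight.

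**The concern.** A test of equality puts the burden of proof on showing a difference. That suits an efficacy claim. A safety claim needs the reverse: the data must rule out a harm of a size that matters. With equality as the null, rejection in the harmful direction would point to harm, and non-rejection leaves the question open. The article states no other criterion by which safety could be shown, so the conclusion envisaged in the Discussion has nothing to rest on except non-rejection.

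Non-rejection is most likely where the trial has least information, that is, for uncommon and serious neonatal events. A real increase in such events could then pass as no difference and be offered as a reason for adoption in labor care. The intention of adequate power for all analyses adds to the risk, because it invites the reader to treat a non-significant neonatal comparison as informative.

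**Working it through.** **1. The plan's own figure.** Inputs from section 3.3: means 46 and 65 min, SDs 39 and 47 min, alpha 0.05, power 0.80, ratio 1:1.

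- Pooled SD = √((39² + 47²)/2) = 43.19; d = 19/43.19 = 0.44.
- Normal approximation, two-sided: n = 2(1.960 + 0.842)²/0.44² = 81.1, so 82 per arm.
- Noncentral t: 82.07, so 83 per arm and 166 in total. This matches the article exactly.
- A one-sided calculation gives 64 to 65 per arm and does not match.

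The figure of 166 is therefore right for a two-sided test of expulsive-phase time. The inputs listed for the other calculations are the active and passive phase times and the VAS. None is a neonatal outcome.

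**2. Power of the planned categorical test.** All 2×2 tables with 83 per arm were enumerated, using Fisher's test when an expected count is below 5 and Pearson's otherwise, two-sided 5%. Power is the sum of the binomial probabilities of the tables with p ≤ 0.05. The baseline rates are assumptions, because the article gives none. Full follow-up is assumed, which favors the plan.

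| Assumed baseline → doubled | Power | Doubling missed |
|---|---|---|
| 2% → 4% | 2.9% | 97% |
| 5% → 10% | 20.8% | 79% |
| 10% → 20% | 43.9% | 56% |
| 15% → 30% | 65.0% | 35% |
| 20% → 40% | 81.4% | 19% |

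Power passes 50% at a baseline of about 11.5%. From 30% to 60% it is about 98%.

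By the normal approximation, 80% power to detect a doubling needs 1,141 per arm at 2%, 435 at 5% and 199 at 10%.

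**3. What the data could still exclude.** With no events among 83 women, the one-sided 95% upper limit for the rate is 1 − 0.05^(1/83) = 3.5%.

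**4. Continuous outcomes (for example arterial pH).**

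- The difference detectable with 80% power is about 0.44 SD.
- With equal SDs, the half-width of the 95% interval for a difference in means is t(0.975; 164) × √(2/83) = 1.975 × 0.155 = 0.31 SD.

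**5. The passages side by side.** Section 2 ties the safety objective to verifying or refuting equality. Section 3.3 fixes 5% and gives no other decision criterion. Section 5 speaks of safety being demonstrated. Of the possible results of that test, only non-rejection points toward safety, and a non-significant p-value does not bound the size of harm.

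**The case against.** Six points can be made for the plan.

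- **The decision rule is not written down.** A reader might infer that the investigators plan to declare the technique safe whenever p > 0.05. The article does not say so, and the Discussion sentence is conditional. This stands: the fault lies in the structure of the hypotheses, not in a stated rule.
- **The p-value is not the only planned output.** Odds ratios and Cohen's d are planned, and reporting is to follow CONSORT. This also stands, and the fix can build on it. Neither effect measure by itself sets a criterion for safety.
- **The size depends on the baseline.** A reader might infer that a doubling would generally be missed. That holds only below a baseline of about 11% to 12%. Section 3.3 gives normal ranges for pH, PaO2, PaCO2, bicarbonate and base excess. If any value outside them counts as abnormal, the outcome could be common and a doubling would probably be found. Apgar and blood gases are also numeric, and for them the limits are the SD figures above.
- **A margin may sit in a fuller document.** The absence of a margin from an article is not the complaint. The hypotheses, the way they are to be judged and the 5% level are already stated, and they are the wrong form for a safety claim.
- **The Discussion claims more than Objective 4 covers.** It refers to mothers and infants, while Objective 4 covers fetal and neonatal outcomes only. This shows that the Discussion sentence needs narrowing.
- **The rest of the trial is untouched.** Randomization, data collection and the efficacy analyses are unaffected, which limits the severity.

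**Conclusion.** The point holds in this form. Objective 4 is a safety objective with an equality null tested at 5%, and non-rejection, the only result that could support a demonstration of safety, cannot do so at any baseline rate. That conclusion needs no assumed figures.

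The size does need them. At 83 per arm, power for a doubling runs from about 3% at an assumed baseline of 2% to about 81% at 20%. For continuous outcomes, differences below about 0.44 SD are detected with less than 80% power. The intention of sufficient power for all analyses is not supported for Objective 4, because no neonatal outcome was used in the sizing, although the 166 itself is correct for expulsive-phase time.

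This should be fixed, but it does not threaten the trial as a whole: it concerns one objective of four and can be put right before results are interpreted.

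**What to change.** - **Section 2, Objective 4:** replace the pair of hypotheses with an estimation aim. For each neonatal outcome, report the between-arm difference, or the odds ratio already planned, with its 95% confidence interval.
- **Section 3.3, Data analysis:** state that p > 0.05 on a fetal or neonatal outcome will not be taken as evidence of safety.
- **Section 3.3, Sampling and Sample Size:** limit the power statement to labor times and VAS.
- **Section 5:** say only which sizes of harm the intervals exclude, and only for the fetal and neonatal outcomes measured.
- **If a safety claim is wanted on one collected outcome:** state in advance, with reasons, the largest worsening that would be acceptable. Make the claim only if the interval excludes it, and confine the claim to that outcome. A margin met on mean pH, for instance, would not rule out a doubling of rare adverse events. For a binary outcome the planned number may be too small: excluding a doubling with equal true rates (one-sided 2.5%, 80% power) would need 299 per arm at an assumed 5%, 142 at 10% and 63 at 20%.

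The estimation wording needs no extra data or participants. The cost is a weaker safety statement than the Discussion now looks forward to.
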